#### Inclusion criteria

Patients registered on the THIN database and aged over 50 on January 1st, 2006.Patients with a recording of TSH above 4.0 mIU/L between January 1st, 2006, and December 31st, 2021.Patients who are prescribed LT4 or receive no hormone replacement therapy. In the cohort study, patients in the treatment group will be prescribed LT4 before the end of the study period, December 31st, 2021. In the emulated target trial study, patients will initiate LT4 treatment and remain on it during a 5-year follow-up between January 1st, 2006, and December 31st, 2021. Patients in the emulated target trial study will be randomly assigned a strategy at baseline and be aware of their assignment.In the cohort study, patient follow-up ends at death, withdrawal from the database or December 31st, 2021, whichever occurs first.

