## Background

Hypothyroidism is a common chronic disease caused by insufficient production of thyroid hormones [1]. Thyroid hormones produced by the thyroid gland regulate metabolism in all tissues, including the heart, liver, brain, muscles, and bones. Any interruption of the thyroid hormone balance can lead to metabolic dysfunction. The overall prevalence of hypothyroidism is approximately 5–10% of the general population in the United Kingdom (UK) [2] and is greater in females and people aged over 60 years [3–5]. Subclinical hypothyroidism (SCH) refers to serum thyroid stimulating hormone (TSH) levels higher than the reference range and levels of free thyroxine (fT4) remaining in the range [1, 6]. Overt hypothyroidism refers to TSH levels being elevated and fT4 levels below their respective reference ranges [7].

Cardiovascular disease remains the leading cause of death worldwide, with ischaemic heart disease and stroke accounting for 8.9 million and 6.1 million deaths, respectively, in 2019 [8]. Each year there are 160,000 deaths in the UK attributed to cardiovascular events [9], accounting for approximately 23.9% of deaths in the UK [10]. Therefore, unnecessary cardiovascular events must be reduced in the population. In addition, the UK population is increasing and ageing; the Office for National Statistics has predicted that by 2043, the number of people aged over 85 will have nearly doubled to 3 million [11]. Due to the ageing and growing population in the UK, a rise in pharmaceutical prescribing can be expected. In 2019, the National Health Service (NHS) distributed 32,956,754 prescriptions of LT4. This is a significant increase compared to only 20,426,378 LT4 prescriptions distributed in 2008 [12]. Moreover, the estimated number of individuals prescribed LT4 in the UK has increased from 2.8 to 4.1% over 11 years. Reducing the number of patients prescribed LT4 will not only potentially improve patient outcomes and quality of life in the ageing population but will reduce prescription wastage, hence cost to the NHS.

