Slightly elevated TSH levels may be beneficial to the older person. Simonsick et al. [17] demonstrated better mobility and cardiorespiratory fitness functioning amongst adults over 70 years, with a mildly elevated TSH between 4.5 and 7.0 mIU/L compared to those with TSH levels of 0.4–4.5 mIU/L [17]. In the Leiden 85 + Study, 599 participants over 85 years old were followed up after four years. Those with a TSH level greater than 4.8 mIU/L had lower mortality than euthyroid individuals with a TSH level within 0.3–4.8 mIU/L; higher levels of fT4 were associated with increased all-cause mortality in the same cohort [18]. On the contrary, the Newcastle 85 + study found no association between higher TSH levels and all-cause mortality in a cohort of 643 patients aged 85 years followed up for 9 years [19]. In addition, a recent narrative review in 2021 found no unfavourable cardiovascular or musculoskeletal outcomes in patients with TSH levels between 4.5 and 7.0 mIU/L [6]. However, a case-control study found a significant mortality increase in patients prescribed LT4 aged over 65 with TSH below 10 mIU/L [20]. Much of the literature, including reviews that are powerful due to tertiary data, suggests that TSH levels between 4.5 and 10 mIU/L may benefit older adults.

However, TSH levels above 10 mlU/L have been found to be detrimental in all patients. A systematic review of 36 studies found an increased incidence of heart failure amongst patients aged over 65 years with TSH levels above 10 mlU/L [21]. Similarly, another systematic review of cohort studies found that in individuals with SCH and TSH levels above 10 mIU/L, there is an increased risk of coronary heart disease events, coronary heart disease mortality and heart failure events [22]. Current evidence indicates that TSH levels above 10 mlU/L can adversely affect older individuals. This is in line with the LT4 prescribing guidelines, stating that the majority of adults should only be prescribed LT4 with TSH levels above 10 mlU/L [23].

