## Methods/Design

### Study aims

The study aims to evaluate whether LT4 benefits patients aged over 50 years with marginally raised TSH. The null hypothesis is that SCH patients over 50 years of age have the same bone health and cardiovascular outcomes when prescribed LT4 compared to those not prescribed LT4. The alternative hypothesis is that SCH patients aged over 50 years of age have worse bone health and cardiovascular outcomes when prescribed LT4 than those who are not prescribed LT4.

The objectives of the study are:

1) To use electronic healthcare records to undertake a cohort study comparing the cardiovascular outcomes (incident diagnosis of angina, myocardial infarction, stroke, peripheral vascular disease and stent/revascularisation procedure) between patients over 50 years of age with mildly elevated TSH levels prescribed LT4 versus those not prescribed LT4.

2) To use electronic healthcare records to undertake a cohort study comparing the bone health outcomes (incident diagnosis of osteoporosis, fragility fractures) between patients over 50 years of age with mildly elevated TSH levels prescribed LT4 versus those not prescribed LT4.

3) To use electronic healthcare records to undertake a cohort study comparing all-cause mortality outcomes between patients over 50 years of age with mildly elevated TSH levels prescribed LT4 versus those not prescribed LT4.

4) To use electronic healthcare records to undertake a target trial emulation study comparing the cardiovascular outcomes (incident diagnosis of angina, myocardial infarction, stroke, peripheral vascular disease and stent/revascularisation procedure) between patients over 50 years of age with mildly elevated TSH levels prescribed LT4 versus those not prescribed LT4 [46].

5) To use electronic healthcare records to undertake a target trial emulation study comparing the bone health outcomes (incident diagnosis of osteoporosis, fragility fractures) between patients over 50 years of age with mildly elevated TSH levels prescribed LT4 versus those not prescribed LT4.

6) To use electronic healthcare records to undertake a target trial emulation study comparing all-cause mortality outcomes between patients over 50 years of age with mildly elevated TSH levels prescribed LT4 versus those not prescribed LT4.

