### Study setting

THIN captures clinical data from general practices across the UK, holding anonymised records of approximately 6% of the UK population from 850 general practices. THIN has over 25 years of data recorded. To ensure a complete and reliable dataset, this project will capture data between January 1st, 2006, and December 31st, 2021. Preliminary counts from THIN show 530,792 patients with a TSH greater than 4 mIU/L. Preliminary counts also show 258,868 patients diagnosed with hypothyroidism within the same period. The variables that will be captured from the THIN database are as follows:

sex,diagnosed with hypothyroidism,date of diagnosis of hypothyroidism,date LT4 treatment commenced,first and last recorded LT4 dose,co-morbidities (heart disease, asthma, chronic obstructive pulmonary disease, diabetes, chronic kidney disease, rheumatoid arthritis, depression, dementia, dyslipidaemia, osteoporosis, fragility fractures).date of diagnosis of co-morbidities,current and past medications,date of death (if applicable),TSH, fT4, thyroxine (T4), triiodothyronine (T3), and free triiodothyronine (fT3) levels,date of recorded TSH, fT4, T4, T3, and fT3 levels,thyroid peroxidase antibody status,body mass index (BMI) at entry and end of the study period,blood pressure,smoking status.

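### Eligibility asks only for a TSH above 4.0 mIU/L, so overt hypothyroidism and, in the cohort study, existing LT4 users are mixed with mild subclinical disease

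*Protocol article*

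**What the plan says.** All statements are in the Protocol article.

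- **Definition (Background).** SCH is "serum thyroid stimulating hormone (TSH) levels higher than the reference range and levels of free thyroxine (fT4) remaining in the range". The contrast follows: "Overt hypothyroidism refers to TSH levels being elevated and fT4 levels below their respective reference ranges". The fT4 result is what separates the two.
- **Target population (Study aims).** "The study aims to evaluate whether LT4 benefits patients aged over 50 years with marginally raised TSH". The hypotheses speak of SCH patients, and all six objectives compare "patients over 50 years of age with mildly elevated TSH levels prescribed LT4 versus those not prescribed LT4". The abstract likewise names subclinical patients.
- **Entry rule (Inclusion criteria).** "Patients with a recording of TSH above 4.0 mIU/L between January 1st, 2006, and December 31st, 2021". The exclusion list repeats this in the negative.
- **Treated group (Inclusion criteria).** In the cohort study, LT4 has to be prescribed before the study period closes on December 31st, 2021, with no order set against the TSH test. In the emulation, treated patients start LT4 and stay on it over a 5-year follow-up.
- **Thyroid-related exclusions.** These are thyroid cancer, pituitary disease, hyperthyroidism, drugs that disturb thyroid function, thyroid surgery or radioiodine, and replacement other than LT4. Overt hypothyroidism and earlier LT4 use are not among them.
- **Analyses by TSH and fT4 (Statistical analysis).** The plan has a subgroup split at TSH 10 mIU/L, a subgroup from 4.0 up to an age-specific limit, sensitivity analyses on the TSH threshold, and a secondary analysis that divides patients at the median fT4.

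**The concern.** The rule for entering the study does not select the population that the study is about. Two kinds of patient satisfy every stated criterion without having untreated SCH at baseline.

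The first is the patient with overt disease. The Background says treatment is accepted practice there, so such patients can be expected to fall more often in the LT4 group. The same applies to high TSH: the guideline as summarised says "the majority of adults should only be prescribed LT4 with TSH levels above 10 mlU/L", and the Background links that range to heart failure and coronary events. Treated patients would then tend to be those with more severe thyroid failure, which is confounding by indication on the primary outcome.

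The second is the long-term LT4 user with one raised TSH while on treatment. In that patient the raised value may only reflect under-replacement, and the condition that led to treatment is unknown. Follow-up would start after the early period of treatment, in people who had already come through it. This is prevalent-user bias, and it arises only in the treated group.

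At stake is whether the main hazard ratio describes the effect of LT4 in the population named in the aims.

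**Working it through.** **1. Set the definition against the criteria**

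| Feature | Definition and aims | Eligibility lists |
|---|---|---|
| TSH | above range; mildly or marginally raised | above 4.0, no upper limit |
| fT4 | within range | no condition |
| Overt hypothyroidism | a separate condition | not excluded |
| LT4 before qualifying TSH, cohort study | not addressed | admitted to treated group |
| LT4 before qualifying TSH, emulation | not addressed | starting LT4 implies new use; no prior-use exclusion |

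**2. Ask whether a planned analysis repairs the main estimate**

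- The split at 10 mIU/L is a subgroup, so patients at 10 or above are in the main analysis. It also leaves low fT4 below 10 untouched.
- The age-specific TSH subgroup and the threshold sensitivity analyses vary TSH only.
- The median fT4 split labels its halves low-normal and high-normal. It presumes an in-range fT4 that eligibility never requires.
- The named confounders are sex, BMI, co-morbidities and smoking, with age and LT4 dosage added in the abstract. Baseline TSH and fT4 are not named.
- The stated intention to deal with immortal time bias concerns time before treatment starts. It does not deal with treatment that began before the qualifying test.

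**3. Size of the contamination**

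The document gives no share of eligible patients with low fT4 or with LT4 before the qualifying TSH, so no figure follows.

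**4. What a stricter definition could cost in power**

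Inputs (Statistical analysis): event rates 4.9% and 5.4%, power 0.9, alpha 5%, taken here as two-sided. With p1 = 0.049, p2 = 0.054, r untreated patients per treated patient, and p̄ = (p1 + r·p2)/(1 + r), the number treated is

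n = [1.960·√((1 + 1/r)·p̄(1 − p̄)) + 1.282·√(p1(1 − p1) + p2(1 − p2)/r)]² / (p1 − p2)²

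- r = 1: n = 41,060 after rounding up (stated 41,059).
- r = 4: n = 25,805 after rounding up (stated 25,804).

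The plan's sample sizes reproduce, so the arithmetic is not at fault. Now suppose that a share f of the minimum sample is lost equally from both groups. The values of f are assumptions. Total records needed are 82,118/(1 − f) and 129,020/(1 − f).

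| Assumed f | Power, cohort / emulation | Total needed for 90% power, cohort / emulation |
|---|---|---|
| 10% | 0.868 / 0.867 | 91,243 / 143,356 |
| 20% | 0.826 / 0.825 | 102,648 / 161,275 |
| 30% | 0.774 / 0.771 | 117,312 / 184,315 |
| 50% | 0.630 / 0.624 | 164,236 / 258,040 |

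The preliminary count of 530,792 patients with TSH above 4 exceeds all of these totals. That count is not stated to be after the age limit or the exclusions, and it does not show how many were on LT4.

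**The case against.** The best defence is that the article consistently calls its patients subclinical, defines that term by in-range fT4, and words the fT4 analysis as if fT4 were normal. On that reading the definition was simply not copied into the list. This may well be the intention, but the lists are explicit enough to name individual drugs, and a data extraction follows the list. The need to reconcile them stands.

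Several stronger readings are tempting, and the document does not support them:

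- **That the cohort is overt disease instead of mild SCH.** Every mild SCH patient with TSH above 4.0 who meets the other criteria still qualifies. The populations are mixed.
- **That both studies admit existing users equally.** The emulation's requirement to start LT4 largely covers this. What is missing there is a stated prior-use exclusion.
- **That a TSH of 10 or more is itself an error of eligibility.** The definition of SCH has no upper limit, and the Background refers to SCH above 10. The tension is only with the unquantified words for mild elevation in the aims, and a split at 10 is already planned.
- **That the share can be read from the counts.** "Preliminary counts also show 258,868 patients diagnosed with hypothyroidism within the same period", and 258,868/530,792 = 48.8%. The two counts are not said to overlap, and a diagnosis code does not establish overt disease. The feasibility practice does not help either: its 622 LT4 recipients are not restricted by TSH or stated age.
- **That positivity fails.** The document does not say that overt patients are almost never untreated, and it notes that prescribing recommendations are not always followed.

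Two further points are fair. The confounder list may not be exhaustive. Requiring a paired fT4 also loses patients and may select on testing behaviour.

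**Conclusion.** The point holds in this form: the stated eligibility rule contradicts the document's own definition of SCH. Followed literally, it admits overt hypothyroidism to both studies and existing LT4 users to the treated group of the cohort study. The main estimate would mix these patients with mild SCH, and no planned subgroup or named adjustment removes them from it.

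The size of the bias cannot be computed from the document. Its net direction is also open: confounding by severity would tend to make LT4 look worse, while including people who have already tolerated treatment could make it look better. The conclusion rests on reading the inclusion and exclusion lists as complete on thyroid status, and on severe disease being treated more often, as the Background implies. It should be settled before the data are extracted.

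**What to change.** Rewrite eligibility for both studies as follows:

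1. Define the index date as the first qualifying TSH above 4.0 mIU/L in the study period.
2. Require fT4 within the laboratory range on that date or within a window set in advance. The window should close before any LT4 is started, so that the value is a true baseline.
3. Require no LT4 prescription before the index date, stated explicitly for the cohort study and the emulation.
4. Keep the broad population with TSH above 4.0 as a sensitivity analysis.
5. Reconcile the aims' wording on mild elevation with the absence of an upper TSH limit. One way is to report the planned split, below 10 against 10 or above, beside the main result.

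TSH, fT4, their dates and the LT4 start date are already on the list of captured variables, so the work is wording and extraction code. The price is that patients without a paired fT4 and prior LT4 users leave the primary set. Before the change is fixed, count the LT4 patients who remain and compare them with the 41,059 needed for the cohort study and the 25,804 for the emulation. If they fall short, report the power that is left.

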The current research group has completed a National Institute for Health and Care Research (NIHR) Research for Patient Benefit study (Study of Optimal Replacement of Thyroxine in ElDerly (SORTED) – a feasibility study: Ref: PB-PG-0610-22139) and has demonstrated that older people can tolerate a lower dose of LT4 and hence higher TSH levels [45]. The work done in 2016 explored the relationship between the three variables: diagnosis of hypothyroidism, TSH measurement, and LT4 treatment. A feasibility analysis at one large rural general practice in Northumberland, England, with a practice list size of 11,752 found that 465 patients had been diagnosed with hypothyroidism. The prevalence of hypothyroidism at the practice was 4%, and the highest prevalence was in the 81–90 years age category, at 9.85%. The female-to-male ratio with hypothyroidism at the practice was 4.4:1.0, such that 379 females had been diagnosed. Despite 465 patients diagnosed with hypothyroidism (Read Coded), 622 patients received treatment with LT4. This is an excess of 157 patients receiving LT4 without a diagnosis of hypothyroidism. This may represent a proportion of SCH patients that are not Read Coded as hypothyroid but are receiving treatment. It is also possible that a small proportion of these patients are hyperthyroid patients receiving block and replace treatment or patients with pituitary disorders. Alternatively, some patients may report symptoms suggestive of hypothyroidism but still have normal serum thyroid function tests and receive LT4 therapy in contravention of accepted clinical practice and guidelines. For this reason, our search strategy centres upon the TSH values recorded in the database rather than a diagnosis. Between 2003 and 2015, 215 (1.9%) patients were recorded as having an age-specific index TSH as mildly elevated, in line with the TEARS study. Of those, 39% were untreated, and 61% were treated with varying degrees of treatment length. This feasibility work concludes that 53% of the treated patients may have been over-diagnosed due to their TSH level being within the range of 4.0 mIU/L and the upper TSH limit given by the TEARS study [13].

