#### Exclusion criteria

Patients aged 50 years or under on January 1st, 2006.Patients without a recording of TSH above 4.0 mIU/L between January 1st, 2006, and December 31st, 2021.Patients diagnosed with thyroid cancer, pituitary disease or hyperthyroidism.Patients prescribed medications such as amiodarone or lithium that can affect thyroid function.Patients who have undergone thyroid surgery or radioiodine treatment, suggesting previous thyroid dysfunction.Patients receiving a different form of thyroid replacement therapy to LT4, e.g. liothyronine or combination therapy with liothyronine and LT4.Patients with a baseline diagnosis of angina, myocardial infarction, peripheral vascular disease or stroke, where cardiovascular is the outcome variable.Patients with a baseline diagnosis of osteoporosis or fracture, where bone health is the outcome variable.

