### Statistical analysis

The sample size calculation is based on the primary outcome of determining a difference in cardiovascular outcomes between patients receiving LT4 or not. The TRUST study of 737 patients aged 65 years and older found a cardiovascular outcome rate of 4.9% in the treatment group and 5.4% in the placebo group. Therefore, based on these outcome rates, for the cohort study, the minimum sample size required is 82,118 patients. Of this sample, 41,059 patients will be prescribed LT4 and 41,059 patients will not be prescribed LT4. A matching ratio of 1:4 (treatment: no treatment) will be used for the target trial emulation study. Therefore, the sample size required is 129,020 patients, with 25,804 patients prescribed LT4 and 103,216 patients not prescribed LT4. This sample size provides a power of 0.9 and alpha of 5%. In both studies, if missing data occurs, multiple imputation methods will be used if up to 40% of the data is missing [47]. Otherwise, pairwise deletion will be used.

In the target trial emulation study, the causal contrasts of interest will be intention-to-treat effect. Chi-square analysis will be used to compare the categorical characteristics of the participants in both studies, such that a p-value of less than 0.05 will be considered significant. Descriptive statistics will be presented. In both studies, the frequency of hypothyroidism diagnosis, smoking status, sex, ethnicity, and location will be given for each group. Survival analysis methods, including Cox proportional hazard models and Kaplan-Meier curves, will be fitted to compare the time to outcome between the groups. The hazard ratios with their 95% confidence intervals will be given.

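### The emulation defines both arms by treatment after baseline, against its own baseline assignment and intention-to-treat contrast, and the cohort study also groups patients on future LT4 use

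*Protocol article*

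**What the plan says.** All the rules on arm membership are in the protocol article under Inclusion criteria.

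- Both studies: "Patients who are prescribed LT4 or receive no hormone replacement therapy". The untreated limb carries no date or window.
- Cohort study: "patients in the treatment group will be prescribed LT4 before the end of the study period, December 31st, 2021".
- Emulated trial, LT4 arm: "patients will initiate LT4 treatment and remain on it during a 5-year follow-up between January 1st, 2006, and December 31st, 2021".
- Emulated trial, assignment: "Patients in the emulated target trial study will be randomly assigned a strategy at baseline and be aware of their assignment".

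Statistical analysis then states that in the emulation "the causal contrasts of interest will be intention-to-treat effect". It also says that immortal time bias will be adjusted for in both studies, and selection and attrition bias in the emulation. The only method named is inverse probability weighting for confounders in the emulation. The listed confounders are sex, BMI, co-morbidities and smoking status.

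**The concern.** An intention-to-treat emulation classifies each patient by treatment at time zero and keeps that label. Later starting or stopping is crossover, and the patient stays in the baseline arm. The Inclusion criteria do the opposite in both arms. The LT4 arm is limited to patients who persist, and the comparator to patients who stay untreated. Starting and stopping LT4 plausibly depend on the course of TSH, on symptoms and on tolerance, so each arm is selected on its own prognosis. The resulting contrast is not the one the article names.

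In the cohort study a patient must survive and remain registered long enough to receive LT4 before entering the LT4 group. That is the usual route to immortal time bias. All-cause mortality, a secondary outcome, is the most exposed.

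**Working it through.** **1. Four patients under the emulation's rules**

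| Patient at time zero | Later course | Arm under intention-to-treat | Arm under Inclusion criteria |
|---|---|---|---|
| No LT4 | Never starts | No LT4 | No LT4 |
| No LT4 | Starts in year 2 | No LT4 | Not a comparator |
| Starts LT4 | Stays on 5 years | LT4 | LT4 |
| Starts LT4 | Stops in year 3 | LT4 | Neither arm |

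Rows 2 and 4 conflict. The article does not say whether the row 2 patient could re-enter the LT4 arm with a later start date. Either way, that patient is missing from the no-LT4 arm.

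**2. The cohort study**

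The row 2 patient has an LT4 prescription before the end of 2021 and so joins the LT4 group. Nobody is dropped, but membership is set by an event after the qualifying TSH.

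**3. The plan's own figure**

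Inputs from Statistical analysis: 4.9% v 5.4%, power 0.9, alpha 5% (two-sided assumed). With a pooled-variance test and no continuity correction,

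n per group = [1.960 √(2 × 0.0515 × 0.9485) + 1.282 √(0.049 × 0.951 + 0.054 × 0.946)]² / 0.005² ≈ (0.6126 + 0.4005)² / 0.000025 ≈ 41,060.

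The plan states 41,059. The same method at 1:4 gives 25,805 and 103,220, against 25,804 and 103,216 stated. The figures reproduce. Arm timing does not enter the formula, so the fix changes none of them.

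**4. Illustration for the emulation comparator**

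Background reports 215 patients with mildly raised TSH in one practice: "Of those, 39% were untreated, and 61% were treated with varying degrees of treatment length". That gives 0.39 × 215 = 83.85 untreated and 0.61 × 215 = 131.15 treated. The share who started late, f, is not given and is assumed here.

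Late starters L = f × 131.15; share of the proper comparator p = L / (83.85 + L).

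- f = 0.10: 13.1 / 97.0 = 13.5%
- f = 0.33: 43.3 / 127.1 = 34.0%
- f = 0.50: 65.6 / 149.4 = 43.9%

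If late starters have r times the event risk of those who stay untreated (assumed), the observed comparator risk divided by the proper one is 1 / [(1 - p) + p r]. With p = 0.34:

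- r = 1.25: 1 / 1.085 = 0.922, about 8% too low
- r = 0.80: 1 / 0.932 = 1.073, about 7% too high

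The planned relative difference is (5.4 - 4.9) / 5.4 = 9.3%. The documents give no figure for patients who stop LT4, so the persistence rule cannot be illustrated in the same way.

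**5. Illustration for the cohort study**

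A simulation with no true LT4 effect used these assumptions: LT4 start rate 0.03 to 0.15 per year, death 0.03 per year, cardiovascular events 0.0108 or 0.02 per year, and follow-up of 1 to 16 years. Between 19% and 59% of patients became LT4 users.

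| Handling of time | Mortality rate ratio, LT4 v none |
|---|---|
| Both clocks from index TSH, ever v never LT4 | 0.31 to 0.46 |
| LT4 clock from LT4 start, comparators never-users | 0.49 to 0.87 |
| Time before LT4 counted as untreated | 0.99 to 1.01 |

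The cardiovascular rate ratio stayed at 0.98 to 1.02, because in this set-up a cardiovascular event does not prevent a later LT4 start.

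**The case against.** The strongest reply is that the sentences describe target-trial strategies: start and stay on LT4, or take none. Strategies of that kind can coexist with an intention-to-treat analysis of baseline assignment. The article is condensed, time-zero rules commonly sit in a fuller document, and adjustment for immortal time and selection bias is promised. Part of this stands. The article does say that assignment is at baseline, and a missing operational detail would not be a finding. But these sentences are placed as eligibility conditions, and as such they contradict the stated contrast. Weighting on the listed confounders does not restore patients whom eligibility has removed.

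A reader might infer four stronger points, which the documents do not support.

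- *That only the comparator is restricted.* The five-year persistence rule limits the LT4 arm as well.
- *That later starters are dropped from both studies.* In the cohort study they move into the LT4 group.
- *That users of menopausal hormone therapy are excluded from the comparator.* The untreated limb omits the word thyroid, but the objectives and Statistical analysis describe the comparator only as patients not prescribed LT4. The Exclusion criteria speak of "Patients receiving a different form of thyroid replacement therapy to LT4, e.g. liothyronine or combination therapy with liothyronine and LT4". Thyroid hormone is plainly meant.
- *That the bias has a known size or sign.* The late-start shares and risk ratios are assumed, and the treated share comes from one rural practice with no timing relative to the index TSH.

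**Conclusion.** The point holds as a contradiction within the article. In the emulation both arms are conditioned on treatment after baseline, while assignment is at baseline and the contrast is intention-to-treat. In the cohort study the grouping uses future LT4 prescriptions, and no stated method deals with the resulting immortal time.

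Size and direction cannot be determined from the documents. The 13.5% to 43.9% of comparators lost and the -8% to +7% shift in comparator risk only show that, on assumed inputs, selection could approach the planned 9.3% difference. The mortality ratios for the cohort study show what is at stake if the promised adjustment is not made; they do not predict the result. The rules should be corrected before the cohorts are built.

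**What to change.** **Emulation.** Define both arms at time zero: LT4 initiated at time zero, against no thyroid hormone prescription on or before time zero. Remove five-year persistence and never-treated status as eligibility conditions. In the intention-to-treat analysis keep later starters and stoppers in their baseline arm, and report both crossover proportions. Both arms must change together. Re-anchoring only the comparator would set it against an LT4 arm still selected on persistence.

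**Cohort study.** Treat LT4 as a time-varying exposure, counting person-time before the first LT4 prescription as untreated.

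**Wording.** Write thyroid hormone replacement in the Inclusion criteria, as a clarification only.

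**Cost.** Wording and cohort-building code. The LT4 start date and medication records are already among the variables to be captured. The downside is that crossover dilutes the intention-to-treat estimate; reporting the crossover proportions makes this visible.
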